### 9.2.3 Assessment of other outcomes of interest

n.a.

### 9.2.4 Assessment of safety outcomes

Safety parameters include the components of the primary outcome: Time to first occurrence of hospitalization; death, initiation of unplanned systemic glucocorticoid therapy, or adrenal crisis.

Safety outcomes will be assessed by telephone on days 7, 28, 35, 90, and 180. Additionally, a subgroup of 180 patients will be seen for a clinical visit on study days 7 and 35. These clinical visits include vital signs (heart rate, blood pressure in recumbent and upright position), and a 250 mcg Synacthen® test.

#### 9.2.4.1 Prednisone side effects

Prednisone side effects are documented as Adverse Events (AEs). According to the official Swiss drug registry published by ([www.swissmedicinfo.ch](http://www.swissmedicinfo.ch)), these include the following: infection, allergic reactions, arterial hypertension, hyperglycemia, psychic symptoms (mood changes, depression, productive symptoms), arterial hypertension, gastrointestinal ulceration, osteoporosis, aseptic bone necrosis, nausea, weight gain, atrophic changes or easy bruising of the skin, erythema, muscle weakness.

These side effects will be recorded as “present” if patients report new or intensified disease-specific pharmacological therapy initiated by their treating physicians or other medical personnel (in the case of infection, allergic reactions, arterial hypertension, hyperglycemia, psychic symptoms, gastrointestinal ulceration, osteoporosis, aseptic bone necrosis), or if patients report them during the interview (in the case of nausea, weight gain, atrophic changes or easy bruising of the skin, erythema, muscle weakness).

Prednisone side effects will be assessed upon enrolment and during each of the visits during the intervention follow-up period (telephone interview or clinical visit, at the time points specified above (please see 9.1., 9.2.1, 9.2.2). They will be recorded on the CRF.

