### 5.2 Secondary Outcomes

1. Time to first occurrence of individual components of the primary outcome;
2. Cumulative overall systemic glucocorticoid dose;
3. Cumulative systemic glucocorticoid dose administered to treat or prevent adrenal failure;
4. Cumulative systemic glucocorticoid dose administered to treat relapse of disease, specified for each disease;
5. General health status as self-assessed by the participant on a visual analog scale (VAS) from 0 to 100, assessed at days 1, 7, 28, 35, 90, 180;
6. Score of symptoms and signs of hypocortisolism: weakness, hypothermia, nausea, vomiting, abdominal pain, fatigue, dizziness (assessed in structured interviews at time points: days 1, 7, 28, 35, 90, 180). Blood pressure (supine and standing) is assessed day 1 in all participants, but due to limited resources only in a subgroup of 180 patients living near their respective study center on days 7 and 35.
7. Performance in 250 mcg ACTH (Synacthen®) test: test assessed day 1 in all participants, plus days 7 and 35 in a subgroup of 180 patients,
8. In patients hospitalized at study entry: length of hospital stay.

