### **8.3 Dose modifications**

The decision to start unplanned open-label glucocorticoid therapy during the blinded treatment phase or during follow-up rests with the treating physician or the patient, not the study team. Indication to do so include flare-up of the underlying disease, symptoms and signs of cortisol deficiency such as weakness, apathy, nausea, vomiting, abdominal pain, hyperthermia, hyponatremia, hyperkalemia, hypoglycemia, or adrenal crisis (i.e. glucocorticoid-responsive shock) (see also section 8.6. below). Should the study physician suspect the necessity of open-label glucocorticoid therapy during follow-up, he/she will contact the treating physician to prompt a visit.

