#### Documenting of AEs

These are documented in SecuTrial as prednisone side effects and include the following: infection, allergic reactions, arterial hypertension, hyperglycemia, psychic symptoms (mood changes, depression, productive symptoms), arterial hypertension, gastrointestinal ulceration, osteoporosis, aseptic bone necrosis, nausea, weight gain, atrophic changes or easy bruising of the skin, erythema, muscle weakness. Additional AE information may be documented in a free text field in SecuTrial.

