#### 11.4.3 Secondary Analyses

Secondary outcomes:

**Performance of the 250 mcg corticotropin stimulation test.** If this test is clinically relevant, it is assumed that in patients with a normal test result, the two study arms will not differ with regard to the primary outcome, whereas patients with a pathological test result will experience an event more often after the rapid termination (experimental arm) than after tapering (control arm). It is thus hypothesized that there is an interaction between the test result and the glucocorticoid withdrawal scheme. To test for a significant interaction, the Cox proportional hazard regression model used to assess the primary objective is extended by the stimulation test result (passed vs. failed) and its interaction with the treatment group (rapid vs. tapering). If a significant interaction is found, subgroup analyses are performed for the two treatment groups in order to estimate the strength of the association between test result and primary outcome.

---

**The time to first occurrence of individual components** of the primary outcome is, in analogy to the (composite) primary outcome, also analysed with Cox proportional hazards regression models.

Cumulative overall systemic glucocorticoid dose, cumulative systemic glucocorticoid dose administered to treat or prevent adrenal failure, cumulative systemic glucocorticoid dose administered to treat relapse of disease (specified for each disease), general health status as self-assessed by the patients on a VAS, blood pressure (supine and standing), hospital length of stay, weakness, hypothermia, nausea, vomiting, abdominal pain, and fatigue are analysed with linear regression models.

In all analyses, the variables for which randomisation was stratified (center and age group) are included as covariates for adjustment. If model assumptions are not met, transformations of outcome variables and the use of generalised linear (instead of linear) models are considered.

Besides the secondary outcomes, potential glucocorticoid-induced side effects will be assessed and documented on the CRF. Proportions of side effects will be compared between treatment groups and analyzed using logistic regression.

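### Interview-reported prednisone side effects count as present even if they predate randomization, which pulls the between-arm comparison toward no difference

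*Protocol*

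**What the plan says.** Section 9.2.4.1 divides the listed prednisone side effects into two groups. Infection, allergic reaction, hypertension, hyperglycemia, psychic symptoms, gastrointestinal ulceration, osteoporosis and aseptic bone necrosis are scored on "new or intensified disease-specific pharmacological therapy initiated by their treating physicians or other medical personnel". The remaining items are scored on report alone: "if patients report them during the interview (in the case of nausea, weight gain, atrophic changes or easy bruising of the skin", with erythema and muscle weakness completing the list. For these there is no condition on onset, worsening or cause.

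The same section provides a baseline: "Prednisone side effects will be assessed upon enrolment and during each of the visits". No stated rule uses it. Section 10.1.2 repeats the list as the adverse events to be recorded: "These are documented in SecuTrial as prednisone side effects and include the following". Section 11.4.3 then plans the comparison: "Proportions of side effects will be compared between treatment groups and analyzed using logistic regression". The covariates it names for all analyses are center and age group; side-effect status at enrolment is not among them.

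Two of the interview items also appear elsewhere with the opposite meaning. The secondary outcomes (5.2) include a "Score of symptoms and signs of hypocortisolism: weakness, hypothermia, nausea, vomiting, abdominal pain, fatigue, dizziness", and section 8.3 names "symptoms and signs of cortisol deficiency such as weakness, apathy, nausea, vomiting, abdominal pain". Section 5.1 lists weakness and nausea among the features that may accompany adrenal crisis.

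**The concern.** Section 7.1 admits only patients with at least 28 days of treatment at an average of 7.5 mg prednisone-equivalent per day or more, and section 6.1 expects many to have had considerably more. Easy bruising, thin skin and weight gain may therefore be present on day 1. A patient who reports such a sign at follow-up is scored the same way whether it arose after randomization or before. Randomization spreads the earlier signs evenly, so they do not favor either arm, but they add the same background to both and shrink the contrast.

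Fewer untoward glucocorticoid effects are part of the potential benefit that section 3.7 claims for the stop arm, as a consequence of the lower cumulative dose. A diluted comparison makes that part of the benefit harder to see.

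A secondary issue is the double listing of nausea and weakness. Section 3.7 names glucocorticoid deficiency and withdrawal syndrome as risks of the stop arm. A stop-arm patient who is nauseated for that reason is recorded under a prednisone label. The causality scale in 10.1.1 is written for serious events, so no stated step separates the two causes.

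**Working it through.** **Plan's own figures.** The protocol gives no figure for the side-effect comparison. Its main design figures reproduce: critical hazard ratio log(0.60 − 0.13)/log(0.60) = 1.478; 206 events by the Schoenfeld formula (two-sided 5%, power 80%); 206/0.40 = 515; 515/0.90 = 572.2, so 573. Side-effect scoring enters none of these.

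**Inputs from the protocol.** The scoring rule (9.2.4.1), prior exposure (7.1), the comparison and its covariates (11.4.3), and 573/2 = 286.5 patients per arm (11.2).

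**Assumed inputs, not in the protocol.** New-onset risk r among patients without the sign at entry: 20% taper, 10% stop. Prevalence at entry b: 0 to 60%, equal in the arms by randomization. A sign present at entry is assumed to be reported at some follow-up interview, equally often in both arms.

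**Dilution.** The scored proportion is p = b + (1 − b)r. The odds ratio (taper versus stop) is [p_T/(1 − p_T)]/[p_S/(1 − p_S)].

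| b | Taper | Stop | Difference | Odds ratio |
|---|---|---|---|---|
| 0 | 0.20 | 0.10 | 10 points | 0.2500/0.1111 = 2.25 |
| 20% | 0.36 | 0.28 | 8 points | 0.5625/0.3889 = 1.45 |
| 40% | 0.52 | 0.46 | 6 points | 1.0833/0.8519 = 1.27 |
| 60% | 0.68 | 0.64 | 4 points | 2.1250/1.7778 = 1.20 |

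The difference shrinks by the factor (1 − b).

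**Second set of assumed rates.** With 15% taper and 5% stop, and 286.5 per arm:

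| b | Taper | Stop | Odds ratio | Power |
|---|---|---|---|---|
| 0 | 0.15 | 0.05 | 0.1765/0.0526 = 3.35 | 0.98 |
| 20% | 0.32 | 0.24 | 0.4706/0.3158 = 1.49 | 0.57 |
| 40% | 0.49 | 0.43 | 0.9608/0.7544 = 1.27 | 0.30 |
| 60% | 0.66 | 0.62 | 1.9412/1.6316 = 1.19 | 0.17 |

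**After the change.** Among patients without the sign at entry the proportions are r itself, so the odds ratio returns to 2.25. If all randomized patients stay in the denominator, p = (1 − b)r. At b = 40% this gives 0.12 and 0.06, and an odds ratio of (0.12/0.88)/(0.06/0.94) = 2.14, still close.

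**Nausea and weakness.** Let a fraction x of an arm report them because of cortisol deficiency, with b = 0, so p = 1 − (1 − r)(1 − x). With the first rates:

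- x = 5%, 10% or 20% in the stop arm only: stop-arm p = 0.145, 0.19 or 0.28; odds ratio 1.47, 1.07 or 0.64.
- x = 10% stop and 5% taper: 0.19 against 0.24; odds ratio 1.35.
- x = 20% in both arms: 0.28 against 0.36; odds ratio 1.45.

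The sign of the result depends on how deficiency symptoms split between the arms, which the protocol does not give.

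**The case against.** The strongest reply is that 9.2.4.1 is a recording rule, not an analysis definition. Enrolment status is collected, section 11.4 defers detail to a statistical analysis plan, and restricting to new onset or adjusting for baseline is routine there. This stands in part: the data exist and such a plan could repair the comparison. But the protocol itself requires new or intensified therapy for one group of items and drops any such condition for the other, then compares the resulting proportions with named covariates that leave enrolment status out. Followed as written, it dilutes.

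A second reply is that an interviewer may in practice ask only about changes since the last contact, most plausibly for weight gain. That would reduce the effect, but the text does not require it.

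On nausea and weakness, a reader might infer that the scoring reverses the benefit of stopping early. The documents do not support that, for these reasons:

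- In a blinded randomized comparison such events count against the arm where they occur, and both symptoms are also analyzed in their own right under 11.4.3, so the harm is not hidden.
- The overlap touches two items; 11.4.3 speaks of proportions in the plural and defines no any-side-effect composite.
- Reversal in the illustration needs deficiency symptoms to be frequent in the stop arm and absent in the taper arm, although taper patients also come off drug by day 28.
- The local-language summary reports the investigators' earlier experience in over 200 patients: targeted questioning about deficiency symptoms showed no difference between those with insufficient and normal test results.
- Section 9.2.4.1 says muscle weakness where the deficiency lists say weakness, although a telephone interview is unlikely to separate them.

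Deleting the two items outright would also be debatable, since 9.2.4.1 takes them from the official drug registry.

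**Conclusion.** The dilution holds. As written, the rule counts interview-reported signs that predate randomization and pulls the side-effect comparison toward no difference; it cannot by itself reverse it. The size depends on prevalence at entry, which the protocol does not give. Over an assumed 20% to 60%, a true odds ratio of 2.25 is scored between 1.45 and 1.20. This assumes that signs present at entry are reported again equally in both arms.

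The double listing of nausea and weakness is a real inconsistency, but a smaller one: it can bias those two items, or an aggregate containing them. The documents do not show that it overturns the overall benefit. Cumulative glucocorticoid dose, the more direct measure of that benefit, is a separate secondary outcome and is untouched.

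**What to change.** In 9.2.4.1 and 11.4.3, count an interview-reported item only if it was absent at the enrolment assessment, preferably with patients free of the sign at entry as the denominator. The alternative is to adjust the logistic regression for enrolment status. If nearly everyone with the sign at entry reports it again, those patients carry almost no information and the adjusted model may be unstable, so the new-onset count is simpler. Align the list in 10.1.2 with the same definition.

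Keep nausea and muscle weakness in the record, but report them by arm as separate items, note that either prednisone or cortisol deficiency may be the cause, and show any aggregate side-effect proportion with and without them.

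The cost is wording. New onset needs no additional data, because enrolment status is already collected. Scoring worsening as well would need a small CRF change if only present or absent is captured.

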#### 9.2.4.2 Laboratory parameters

In menstruating females willing to participate in the trial, a urine pregnancy test will be performed at the screening

---

visit.

In all trial participants, a 250 mcg Synacthen® test will be performed on study day 1. Results will be concealed until the end of the trial.

In all trial participants, the serum remaining from the basal cortisol measurement will be frozen at -20°C as reserve for later batch analyses.

In a subgroup of 180 patients the 250 mcg synacthen test as well as the storage of 5 ml reserve serum will be repeated on study days 7 and 35.

#### **9.2.4.3 Vital signs**

Blood pressure and heart rate in lying and supine position after at least 5 minutes resting will be measured in all participating patients on study day 1. The same measurements will be repeated in a subgroup of 180 patients on days 7 and 35.

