## 9. STUDY ASSESSMENTS

### 9.1 Study flow chart(s) / table of study procedures and assessments

| Study Periods                                                                                                                                                           | Screening  | Treatment, Intervention Period |              |               | Follow-up     |                |                |
|-------------------------------------------------------------------------------------------------------------------------------------------------------------------------|------------|--------------------------------|--------------|---------------|---------------|----------------|----------------|
| Visit                                                                                                                                                                   | 1          | 2                              | 3            | 4             | 5             | 6              | 7 (final)      |
| Time (hour, day, week)                                                                                                                                                  | -7d to -1d | Day 1                          | Day 7
±1d | Day 28
±3d | Day 35
±3d | Day 90
± 5d | Day 180
±7d |
| Patient Information and Informed Consent                                                                                                                                | x          |                                |              |               |               |                |                |
| In- /Exclusion Criteria                                                                                                                                                 | x          |                                |              |               |               |                |                |
| Vital Signs (heart rate, blood pressure), body weight, height [only day 1])                                                                                             |            | x                              | x **         |               | x **          |                |                |
| Laboratory Tests:
250 mcg Synacthen® test                                                                                                                            |            | x                              | x **         |               | x **          |                |                |

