### 9.2 Assessments of outcomes

#### 9.2.1 Assessment of primary outcome

Assessment tools of 1° outcome measures:

- Questionnaire: Hospitalization? Unplanned glucocorticoid therapy? Adrenal crisis?
- Treating physician interview: Death?

The 1° outcome can be assessed during a telephone interview with the patient using a questionnaire.

If a patient cannot be reached, the treating physician will be contacted to inquire about the possibility of the patient's death.

The 1° outcome will be assessed by telephone on days 7, 28, 35, 90, and 180; ± the variations indicated in the study flow chart. Additionally, a subgroup of 180 patients living near their respective trial site will be seen for a clinical visit on study days 7 and 35. These clinical visits include vital signs (heart rate, blood pressure in recumbent and upright positions), and a 250 mcg Synacthen® test.

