#### Assessment tools of 2° outcome measures:

- Questionnaire: individual components of 1° outcome; SF-12 survey; symptoms of hypocortisolism
- Signs of hypocortisolism, in subgroup as specified in above table: measure blood pressure (supine and standing), measure heart rate.
- Treating physician interview: cumulative systemic overall glucocorticoid dose? Cumulative systemic glucocorticoid dose to treat or prevent adrenal failure? Cumulative systemic glucocorticoid dose to treat relapse of underlying disease?
- Perform 250 mcg ACTH (Synacthen®) test\*: in subgroup as specified in the above table.
- Measure HbA1c value: in subgroup as specified in the above table.
- Determine length of hospital stay (if hospitalized upon study inclusion): Study hospital chart

\*The 250 mcg ACTH (Synacthen®) test is a routine procedure for the assessment of the functional status of the hypothalamus-pituitary-adrenal axis. The test is performed as follows. It can be done at any time during the day without the need of a fasting state. A blood sample is drawn for measurement of baseline serum cortisol. 1 ampoule (250 mcg) of tetracosactide (beta-1-24 – corticotropin; Synacthen®) is injected intravenously. 30 and 60 minutes after the injection, blood samples are drawn for measurement of stimulated serum cortisol.

The 2° outcomes will be assessed by telephone on days 7, 28, 35, 90, and 180. Additionally, a subgroup of 180 patients will be seen for a clinical visit on study days 7 and 35. These clinical visits include vital signs (heart rate, blood pressure while in recumbent and upright position, and a 250 mcg Synacthen® test.

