### **9.3.2 Day 1 (visit 2)**

Measure heart rate and blood pressure in recumbent and supine position after at least 5 minutes resting. Randomize patient. Perform 250 mcg Synacthen® test. Draw blood for reserve serum. For reserve serum: centrifuge sample, pipet serum into 1 ml aliquots, store at -20°C. Assess VAS for general health status. Fill out CRF. Dispense trial medication. Schedule visit 3.

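### Four procedure lines (9.2.4.3, 9.3.2, 9.3.3, 9.3.5) name the lying posture twice, so no procedural line orders the standing blood pressure that 5.2 requires on day 1

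*Protocol*

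**What the plan says.** The outcome and analysis text asks for two postures. Section 5.2, item 6, states "Blood pressure (supine and standing) is assessed day 1 in all participants", with repeats on days 7 and 35 in a subgroup of 180. The tool list in 9.2.2 has "Signs of hypocortisolism, in subgroup as specified in above table: measure blood pressure (supine and standing". Section 11.4.3 lists supine and standing blood pressure among the outcomes for linear regression.

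The descriptions of the subgroup's clinical visits agree with this. Section 9.2.1 has "vital signs (heart rate, blood pressure in recumbent and upright positions", and 9.2.2 has "vital signs (heart rate, blood pressure while in recumbent and upright position". Section 9.2.4 says the same.

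The lines that tell staff what to do at a visit differ. Section 9.2.4.3 says "Blood pressure and heart rate in lying and supine position after at least 5 minutes resting will be measured in all participating patients" on day 1, and adds "The same measurements will be repeated in a subgroup of 180 patients on days 7 and 35". The day-1 step in 9.3.2 reads "Measure heart rate and blood pressure in recumbent and supine position after at least 5 minutes resting", and the same instruction stands in 9.3.3 (day 7) and 9.3.5 (day 35). The flow-chart row in 9.1 reads "Vital Signs (heart rate, blood pressure), body weight, height [only day 1" and names no posture.

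On adjustment, 11.4.3 says that all analyses include center and age group as covariates. It does not mention the day-1 value of the outcome.

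**The concern.** Lying, recumbent and supine all describe a patient lying down. Read literally, the four procedure lines ask for the same posture twice, and a site that follows them takes no standing reading. The condition of at least 5 minutes' rest is attached to both readings. That suits a lying measurement but does not say when after rising a standing one is to be taken.

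This is a data-collection problem, so leaving it to a later analysis plan does not help. Where the standing value is missing, half of this secondary outcome cannot be analysed for that patient. Section 4.3 makes the relation between signs of hypocortisolism and biochemical adrenal performance a secondary objective. Day 1 is the only occasion on which every participant has both blood pressure and the ACTH test, and it is where the instruction is weakest.

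A smaller matter is that 11.4.3 does not name day-1 blood pressure as a covariate, although it is measured in everyone. Follow-up readings come from only 180 patients.

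**Working it through.** **Instructions side by side**

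| Protocol section | Applies to | Postures named |
|---|---|---|
| 5.2, item 6 | day 1 in all; days 7 and 35 in the subgroup | supine, standing |
| 9.2.2, tool list | subgroup | supine, standing |
| 9.2.1, 9.2.2 (visit text), 9.2.4 | subgroup visits, days 7 and 35 | recumbent, upright |
| 11.4.3 | analysis | supine, standing |
| 9.1, schedule row | day 1 in all; days 7 and 35 in the subgroup | none |
| 9.2.4.3 | day 1 in all; days 7 and 35 in the subgroup | lying, supine |
| 9.3.2 | day 1 in all | recumbent, supine |
| 9.3.3 and 9.3.5 | subgroup, days 7 and 35 | recumbent, supine |

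**Day 1.** The two procedural lines, 9.2.4.3 and 9.3.2, both omit standing. The schedule is silent on posture, and the other lines that order an upright reading concern the subgroup. Only 5.2 asks for it.

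**Days 7 and 35.** Sections 9.2.1, 9.2.2 and 9.2.4 order an upright reading; 9.2.4.3, 9.3.3 and 9.3.5 do not. The instructions conflict, but standing is explicitly ordered somewhere.

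**Count of planned standing readings** (573 from 11.2, 180 from 5.2; drop-out ignored)

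- Day 1, no procedural line orders standing: 573.
- Days 7 and 35, conflicting lines: 180 × 2 = 360.
- Total planned: 573 + 360 = 933.

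These figures count readings that depend on unclear text. They are not an estimate of readings lost.

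**Day-1 covariate.** Assumptions, none of them in the protocol: the 180 split evenly, 90 per arm; the correlation r between the day-1 and follow-up values is 0.3, 0.5 or 0.7; the comparison is with a model that has no covariates.

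- Unadjusted standard error of the arm difference: SD × √(2/90) = 0.149 SD.
- With the day-1 value it is multiplied by √(1 − r²). The sample size that would give the same precision without the covariate is 180/(1 − r²).

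| r | √(1 − r²) | Interval narrower by | Equivalent n |
|---|---|---|---|
| 0.3 | 0.954 | 5% | 198 |
| 0.5 | 0.866 | 13% | 240 |
| 0.7 | 0.714 | 29% | 353 |

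The planned model already adjusts for center and age group. If these explain part of the correlation, the further gain is smaller than the table shows.

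**The case against.** The best reply is that this is a wording slip with a clear intent. An instruction to measure in two positions makes no sense if both are lying, and every other section that names a posture says standing or upright. For days 7 and 35 the upright reading is ordered in three places. The case report form, which is not shown, may have a field for standing pressure. Most of this stands. A reader might infer that all 933 readings are at risk, or that sites took no standing readings. The documents support neither: the 360 follow-up readings are explicitly ordered elsewhere, and nothing shows what sites did. What the reply does not remove is that the slip recurs in all four operational lines and that, on day 1, no procedural line corrects it.

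On the covariate, section 11.4 leaves detailed methods to a statistical analysis plan, and naming two covariates does not rule out a third. That is fair. The covariate point would not stand alone and is offered only as an addition. A reader might also infer that leaving out the day-1 value biases the comparison between arms. It does not, because allocation is randomised; only precision is given up.

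**Conclusion.** The contradiction holds and is minor. Four procedure lines name one posture twice, against 5.2, 9.2.2 and 11.4.3 (supine and standing) and against 9.2.1 and 9.2.4 (recumbent and upright at the subgroup visits). The gap is substantive on day 1, where 573 planned standing readings rest on the outcome list alone; on days 7 and 35 it is a conflict between sections. How many readings were or will be missed cannot be determined from the protocol.

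It would be wrong to infer that the primary result is at risk. The primary outcome uses blood pressure only through adrenal crisis, defined in 5.1 as glucocorticoid-responsive hypotension or shock, and does not depend on these scheduled readings. The effect is limited to a secondary sign.

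The text conflict rests on no assumption. The size of the covariate gain rests on the assumed correlations, the even split and the covariate-free comparator.

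**What to change.** In 9.2.4.3, 9.3.2, 9.3.3 and 9.3.5, replace the paired postures by: supine after at least 5 minutes' rest, then standing, at a stated time after rising. Naming the posture in the schedule row of 9.1 would also help.

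In 11.4.3, as a minor addition, include the day-1 value of the same measure as a covariate: day-1 supine for supine pressure on days 7 and 35, and day-1 standing for standing pressure.

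The cost is rewording four lines and adding one sentence to the analysis section. No new visit is needed, and the standing reading takes a few minutes. The change cannot restore readings already missed: the first participant was scheduled for June 2017 and this version is dated August 2021, so some day-1 standing values may be missing for good.
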